#### **4.6 SAFETY CONSIDERATIONS**

As mentioned in section 4.5, all patients will be risk stratified for risk of cardiac events during exercise therapy. The risk stratification checklist is attached as an appendix (1) to this document. All patients classified as high risk will be excluded from participation in the study. In addition, only CR trained and registered Physiotherapists will be employed to administer the CR intervention to these patients. Furthermore, all patients will be assessed (BP, PR and general wellbeing) before and after each exercise therapy session to ensure that they are safe to exert and to exit the clinic soon after the therapy session respectively. Additionally, the study will only enroll patients who are also on secondary prevention medications; and therapists will ensure that all enrolled participants are adhering to their medications on each session day. Finally, one guardian for each patient will be trained on how they can supervise a prescribed home exercise program to ensure that patients exert safely at home. In case an adverse event such as syncope, cardiac arrest or sudden death has been recorded amongst the study population within 24 hours of exercise therapy, a proper documentation will be done and the case will be thorough investigated to ascertain if exercise therapy is indeed the cause. This and all proceedings of the investigations will also be reported to COMREC immediately in writing. In a situation where the causation is ascertained and exercise therapy is found to be at fault, the intervention will be terminated.

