### ***Specific Objectives:***

1. To describe improvements in cardiovascular function at rest and on exercise among patients with a diagnosis of CHF
2. To describe the frequency of hospitalization among patients diagnosed with CHF enrolled into the cardiovascular rehabilitation program (CRP).
3. To describe the challenges that may be associated with establishment of a CRP at the QECH.

**Study design, population, sample size and sampling strategy:** This will be a prospective open label clinical trial of patients being discharged from the medical wards at QECH with a diagnosis of CHF. There will be two arms in the study with a total of 80 participants; Arm 1 will comprise of 40 patients with CHF who will receive cardiovascular rehabilitation as an intervention of interest, along with the usual cardiac medications that also include secondary prevention drugs, while 40 patients with CHF in arm 2 will be on cardiac medications that also include secondary prevention medications and education but not the exercise component of cardiac rehabilitation. Each participant will pick unlabelled sealed envelope with a paper that has a number that will determine to which group he or she will belong to. Participants will be followed up for 24 weeks. Participants in arm 1 will have regular cardiovascular exercise training once a week for 12 weeks and followed up without active exercise training for another 12 weeks. Arm 2 participants shall receive education component of cardiac rehabilitation at baseline and during the time points they will come for screening. Participants in both arms 1 and 2 will

continue to take cardiac medications as per their cardiologist's prescription throughout the study period.

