While participants in the Arm 1 of the trial receive both treatment modalities of CR (counselling/education and exercise therapy) and their cardiologists' prescribed cardiac medications, participants in the Arm 2 will receive the prescribed cardiac medications and education about their condition (nature of disease, risk factor modification, compliance to medications, nutritional needs); participants in Arm 2 (the control group) will come at baseline, and after 4, 8, 12 and 24 weeks for assessment and education. Figure 2 illustrates the circuit training program that will be followed during the therapy sessions. The exercise session will start with a warm up session and end with a cool down session; both sessions will be done in a group. The Arm 1 participants shall be asked to carry out two therapy sessions for each week at home, and attend a session each week at the hospital. This will assist in reducing the travel costs and avoid losses to follow up. Nevertheless, supervision at home is essential to ensure safety of the patients and efficacy of the treatment at home. Therefore, one guardian for each participant will be trained on how they will supervise the therapy sessions at home. A one-day training for the guardians will be given. All patients will be given the same home-therapy program; box stepping, walking and jogging for a predetermined FITT based on each participants' exertion capacity. The intervention will be delivered over a 12 weeks' period; participants will visit the hospital once a week and perform the rest of therapeutic tasks at home on two extra days per week for the 3 months. After the twelve-week period, all participants will be followed up for a period of twelve more weeks. All COVID-19 preventive measures namely; hand hygiene, social distance and surface/equipment disinfection will be observed. Therapists will use surgical masks during exercise therapy sessions, and patients will be asked to put on the masks before and after the exercise therapy session because they may not be able to breath while exerting.

**Table 1.** The reference benchmark for exercise prescription

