|                                                                            | Frequency                   | Intensity                                                                             | Time                                                                                 | Type                                                                                                    |
|----------------------------------------------------------------------------|-----------------------------|---------------------------------------------------------------------------------------|--------------------------------------------------------------------------------------|---------------------------------------------------------------------------------------------------------|
| Cardiovascular Training
(exercises to enhance cardiovascular endurance) | 3 times a week for 12 weeks | 40-70% Heart Rate Reserve (HRR)
12-14 Rating of Perceived Exertion (RPE)           | 55 minutes (15 minutes warm up, 30 minutes conditioning phase, 10 minutes cool down) | Aerobics (treadmill, board stepping, cycling, point marching)                                           |
| Strength training
(Exercises to improve muscular strength)              | 2 times a week for 12 weeks | 30-70% 1 Repetition Maximum (1RM)
(30-40% 1RM: upper body, 50-60% 1RM: lower body) | 2-4 sets of 10-15 repetitions                                                        | Resistant exercises
(8-10 different muscle groups: weight lifting and pulleys, thera-band stretches) |

[figure not shown]

**Figure 2:** A circle showing the stages which will be followed during the delivery of exercise therapy, a component of CR intervention

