#### Appendix 4: Cardio-respiratory parameters

**ID:**

**Initials:**

| PARAMETERS                                           | BASELINE | 4 WEEKS | 8 WEEKS | 12 WEEKS | 16 WEEKS | 24 WEEKS |
|------------------------------------------------------|----------|---------|---------|----------|----------|----------|
| Blood Pressure                                       |          |         |         |          |          |          |
| Heart Rate                                           |          |         |         |          |          |          |
| O 2 sats                                  |          |         |         |          |          |          |
| Exercise tolerance capacity                          |          |         |         |          |          |          |
| Challenges                                           |          |         |         |          |          |          |
| Number of hospital admissions (reason for admission) |          |         |         |          |          |          |

PATIENT ID:.....

HR AT REST.....

BETA-BLOCKED?:.....

HRMAX:.....

HRR:.....

70%HRR:.....

| STAGES | HEART RATE | METS
ACHIEVED | OXYGEN
SATURATION | RPE |
|--------|------------|------------------|----------------------|-----|
| 1      |            |                  |                      |     |
| 2      |            |                  |                      |     |
| 3      |            |                  |                      |     |
| 4      |            |                  |                      |     |
| 5      |            |                  |                      |     |

TEST COMPLETED? YES NO

REASON FOR TERMINATION:.....  
 .....  
 .....  
 .....

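### The adverse-event rule in section 4.6 is tied to exercise sessions, so it covers no Arm 2 time and about 21% of Arm 1 follow-up, and deaths, arrests and syncope outside hospital have no stated capture in either arm

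*Protocol*

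**What the plan says.** Section 4.6 holds the adverse-event procedure in the protocol text at hand. It gives syncope, cardiac arrest and sudden death as examples and applies when such an event "has been recorded amongst the study population within 24 hours of exercise therapy". What follows is that "a proper documentation will be done and the case will be thorough investigated to ascertain if exercise therapy is indeed the cause", with immediate written notice to the ethics committee. If exercise is found to be at fault, the intervention ends.

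For Arm 1, section 4.5 asks for "two therapy sessions for each week at home, and attend a session each week at the hospital", and Table 1 sets cardiovascular training at "3 times a week for 12 weeks". The study design paragraph of the executive summary states "Participants will be followed up for 24 weeks", and says that Arm 1 is "followed up without active exercise training for another 12 weeks" once training ends. Arm 2 receives medication and education without the exercise component.

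A second channel exists. Section 4.7 has all parameters and hospital admissions recorded at 4, 8, 12, 16 and 24 weeks. Appendix 4 has a row that begins "Number of hospital admissions (reason for admission", so it takes a count and a reason at each time point. Its other rows are blood pressure, heart rate, oxygen saturation, exercise tolerance and challenges. There is no row for death or vital status, and none for syncope or arrest without admission.

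**The concern.** The 4.6 rule is worded for the whole study population, but its clock starts with an exercise session. A control participant has no session, so nothing that happens in Arm 2 can trigger it. The same is true of Arm 1 in weeks 13 to 24. If the plan is followed as written, the two arms are watched with unequal intensity for the events that matter most to safety.

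Two consequences follow. First, an Arm 1 syncope soon after exercise is written up, while the same syncope in a control at home may leave no trace. A tally from the 4.6 records would then show events in Arm 1 alone, even if the risk were the same in both arms. Second, objective 2 is the frequency of hospitalization, and the executive summary expects fewer admissions in Arm 1. A participant who dies at home can have no further admissions. Without a record of the death, the blank columns on Appendix 4 look the same as loss to follow-up, which section 9.0 anticipates.

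This concerns which data are collected. An analysis plan cannot recover events that were never recorded.

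**Working it through.** The protocol states no figure for the reach of the 24-hour rule, so there is none to reproduce. The share below follows from the schedule.

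**Inputs**
- Sessions per week in Arm 1: 1 at hospital + 2 at home = 3 (section 4.5, Table 1).
- Training period: 12 weeks = 84 days (section 4.5).
- Follow-up: 24 weeks = 168 days (executive summary).
- Window: 24 hours per session (section 4.6).
- Exercise sessions in Arm 2: 0.

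**Share of follow-up covered, with non-overlapping windows**
- Arm 1: 3 × 12 = 36 windows of one day. 36 / 168 = 21.4% (in hours, 864 / 4,032).
- Arm 1, training weeks only: 36 / 84 = 42.9%.
- Arm 1, weeks 13 to 24: 0 / 84 = 0%.
- Arm 2: 0 / 168 = 0%.

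**Sensitivity of the Arm 1 figure**
- Adding the 55-minute session to each window: 36 × (24 + 55/60) / 24 / 168 = 22.2%.
- Counting only the 12 hospital sessions: 12 / 168 = 7.1%.
- Placing the two weekly strength sessions of Table 1 on separate days, 5 × 12 = 60 windows: 60 / 168 = 35.7%. The 1 + 2 weekly schedule in 4.5 does not support this reading.

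The Arm 2 figure is 0% under every reading.

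**Illustration of unequal capture.** The protocol gives no event rate, so the 24-week risk p is an assumption. It is taken as equal in both arms with a constant hazard, and there are 40 participants per arm. Expected events per arm = 40 × p. Expected to meet the 4.6 trigger in Arm 1 = 40 × p × 36/168.

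| Assumed p | True events per arm | Meet the trigger, Arm 1 | Meet the trigger, Arm 2 |
|---|---|---|---|
| 5% | 2.0 | 0.4 | 0 |
| 10% | 4.0 | 0.9 | 0 |
| 20% | 8.0 | 1.7 | 0 |

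The table describes the 4.6 rule alone. Some of the remaining events would lead to admission and be seen on Appendix 4.

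**Stated capture, by type of event**
- Event leading to admission: Appendix 4, both arms, at scheduled time points.
- Syncope or arrest without admission, or death outside hospital, within 24 hours of exercise: section 4.6, Arm 1 only.
- The same events at any other time, or in Arm 2: nothing stated.

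The admissions channel has a limit of its own. Section 4.5 lists Arm 2 visits at baseline and 4, 8, 12 and 24 weeks, while 4.7 and Appendix 4 include week 16. An Arm 2 admission after week 12 could still be picked up at week 24, but only if the participant attends.

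**The case against.** The strongest reply is that 4.6 is a trigger for causality review and urgent reporting, and that closeness to exercise is a natural trigger for asking whether exercise was the cause. The text does not say that other events go unrecorded. Causality is to be judged by investigating each case, not by comparing counts. Admissions are taken in both arms with reasons, and an in-hospital death would ordinarily involve an admission. Home sessions are supervised by a trained guardian. The pilot's three specific objectives do not include a comparison of all adverse events.

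Most of this stands, and it sets the limits of the point. A reader might infer that serious events are documented only inside the window, or that no safety comparison between arms is possible. The documents support neither: 4.7 and Appendix 4 record admissions with their reason whatever the arm or the timing of exercise. The 21.4% therefore measures the reach of the 4.6 rule, not of all serious-event recording. Half of its denominator has no training by design, which is why the 42.9% is given beside it.

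What the reply does not answer is the gap between the two channels. A control who faints at home, or a participant in either arm who dies outside hospital away from a session, falls under neither. The challenges row of Appendix 4 does not help, since 4.7 uses it for obstacles to following home exercise and nutrition advice. Appendix 4 is completed at visits that a participant who has died cannot attend, and no other source is named. Objective 2 also makes the point relevant without a wider safety aim, because admission counts need to be read beside deaths.

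**Conclusion.** The point holds in this form. The documentation and reporting rule in 4.6 covers 0% of Arm 2 follow-up and about 21% of Arm 1 follow-up (36 of 168 days), or about 43% of the training weeks. Admissions can be compared between arms. Deaths outside hospital, and syncope or arrest without admission, cannot, because outside the Arm 1 windows neither arm has a stated means of recording them.

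The percentages assume three sessions a week on separate days, all attended, and count home sessions as exercise therapy. The size of any distortion in objective 2 cannot be given, since the protocol states no death or admission rate. The gap should be closed, because the record cannot be rebuilt reliably afterwards and the change is small.

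**What to change.** In 4.6, add one sentence: every death, cardiac arrest and syncope is recorded in both arms from allocation to week 24, with its date and, in Arm 1, the time since the last exercise session. In Appendix 4, add two rows, one for vital status with date of death and one for syncope or cardiac arrest with date. Report the counts by arm next to the admission counts.

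Leave the existing 24-hour trigger for causality investigation, ethics reporting and termination as it stands. The addition concerns recording only.

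Reconcile the Arm 2 visit list in 4.5 with the week 16 time point in 4.7 and Appendix 4, so that both arms are asked on the same schedule.

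The cost is a little more recording at visits that already take place, plus a status check, for example with the guardian or family, for participants who do not attend.

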#### **4.7 Data Collection**

A manual sphygmomanometer will be used to measure BP, Oximeter will be used to measure Oxygen saturations. PR will be checked manually by feeling the radial artery using the third and index fingers Risk stratification will be done using the BACPR stratification forms (Appendices 1-2). Exercise testing will be conducted using **Chester step test for prescription (Appendix 9)**, and **exertion tolerance capacity will be checked using 6-minute walk test**; more details on 6-minute walk test can be accessed using this link (<https://doi.org/10.1164/ajrccm.166.1.at1102>) (24), and outcomes of 6-minute walk test will be recorded using the form attached as an appendix (Appendix 3).

As aforementioned, patients will be screened at baseline before being enrolled into the CRP. At baseline, the following descriptive data will be collected; BP, PR, O2sats and exercise capacity.

Additionally, data on risk stratification for disease progression and occurrence of cardiac events during exercise therapy will be recorded at baseline. BP and PR will be checked before and after each session for safety purposes **(Appendix 12)**; patients will also be asked, on each hospital therapy day, about the challenges faced that may be negatively contributing to adherence of the home exercise and nutrition interventional advice given to be followed at home. All parameters, including incidents of hospital admissions, will also be examined and recorded at 4, 8, 12, 16 and 24 weeks. **The Physiotherapists will record challenges they experienced at all stages of this project; from enrolment of study participants to discharge (Appendix 11).** The data will be collected on paper, and transferred onto Microsoft excel sheet on a computer.

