**Exclusion criteria**

- a. Failure to provide informed consent form
- b. Not willing to return for follow up visits
- c. Physical impairment that would affect participation in physical activity
- d. Coming from outside Blantyre
- e. Patients classified as high risk for cardiac events during exertion

**Data management and analysis:** Descriptive analysis will be conducted using SPSS software; frequencies and mean changes with standard deviations and confidence intervals will be used to report the effect size of the intervention. Multivariate paired T tests will be conducted to compare the changes in each variable at the five time points, and **independent t-test will be conducted to compare the changes between the two groups.** Tables and graphs will be used to present the findings.

Expected outcomes: Participants in arm 1 will have better cardiovascular function and fewer hospital admission compared with the controls during the first 12 weeks and that these benefits will remain at 24 weeks.

**Dissemination plans:** Findings from the study will be presented to QECH management and clinicians involved in managing patients with CHF. The findings will also be presented at the COMREC dissemination conference. Furthermore, the results will be submitted to a peer review journal for publication.

***Anticipated challenges:*** It is anticipated that patients may be lost to follow up and discontinue with the prescribed intervention due to transportation related costs. Therefore, the patients enrolled in this program will be assisted with the transportation costs; patients enrolled will be those who will manage to travel the distance with the allowance given. In addition, patients will be asked to come for a therapy session at the hospital once each week and do the other two sessions at home with a trained family member.

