### 3.2 Specific Objectives

1. To describe the improvements in cardiovascular function among patients with CHF following administration of CR
2. To describe the frequency of hospitalization among patients diagnosed with CHF
3. To describe the challenges that may be associated with establishment of a CRP at QECH

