## **6.0 Analysis and presentation of results**

The SPSS software will be used to analyze this data. Frequencies and mean changes with standard deviations will be used to descriptively illustrate the effect size of the intervention. Paired t-tests will be carried out to compare and show the changes in the variables at the start of the program and after 3 and 6 months of CR reception. **Independent t-tests will be carried out to compare results between the two groups.** Tables and graphs will be used to present the findings.

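### Hospital admissions are recorded only as counts per visit, without all-cause death or exit dates, so unequal death or dropout between arms would distort the comparison

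*Protocol*

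**What the plan says.** Objective 2 in section 3.2 is descriptive: "To describe the frequency of hospitalization among patients diagnosed with CHF". The Executive summary, under expected outcomes, goes further and predicts a difference between arms: "Participants in arm 1 will have better cardiovascular function and fewer hospital admission compared with the controls during the first 12 weeks". It expects that benefit to persist at 24 weeks.

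Section 4.7 has all parameters, "including incidents of hospital admissions, will also be examined and recorded at 4, 8, 12, 16 and 24 weeks". The matching row of Appendix 4 is a count, "Number of hospital admissions (reason for admission", with one column per visit. That form has no row for death, withdrawal or date of last contact.

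On analysis, section 6.0 names frequencies and mean changes as descriptive summaries, and then: "Independent t-tests will be carried out to compare results between the two groups". The Executive summary words the same step as "independent t-test will be conducted to compare the changes between the two groups". Neither sentence mentions admissions.

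Death appears once, in section 4.6. An event such as syncope, cardiac arrest or sudden death is documented and investigated if it "has been recorded amongst the study population within 24 hours of exercise therapy". Arm 2 has no exercise component.

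Losses are foreseen in section 9.0, and section 4.4 allows 5% dropout. Table 4 pays for 15 hospital visits per Arm 1 patient and 4 per Arm 2 patient. Section 4.5 brings controls in at baseline and at 4, 8, 12 and 24 weeks, without week 16.

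**The concern.** A patient with heart failure who dies or leaves in week 3 cannot be recorded with later admissions. On Appendix 4 that patient leaves blank columns and nothing to say why. If the totals are then compared as they stand, the arm with more early exits shows fewer admissions even when the true admission rate is the same.

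The admission comparison is one of the two clinical benefits that the Protocol expects to show. It would be hard to read without knowing how many patients in each arm died and how long each was observed. The choice of model can be left to a statistical analysis plan, but such a plan cannot recover vital status and exit dates that were never collected.

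**Working it through.** **What the Protocol supplies.** It states no admission rate, death rate or exit rate by arm. Its sample size (40 per arm for a difference of 0.6) is not linked to admissions, so there is no stated figure for this outcome to reproduce. The visit budget does reproduce: 40 × 15 + 40 × 4 = 600 + 160 = 760 paid visits, as in Table 4.

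**Who can be recorded as dead.**
- Arm 1, weeks 0-12: only a sudden death within 24 hours of exercise therapy.
- Arm 1, weeks 12-24: almost none, because active training has stopped.
- Arm 2, any time: none, because there is no exercise therapy to start the 24-hour window.

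**Exit unrelated to prognosis.** Assume the same true admission rate r per 24 weeks in both arms, a proportion d leaving early, and leaving times uniform over follow-up. The expected count per patient is r(1 − d/2), so r cancels and

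ratio of mean counts (Arm 1 : Arm 2) = (1 − d1/2) / (1 − d2/2).

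With d2 = 5% the denominator is 0.975:

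| Arm 1 exit | Calculation | Ratio |
|---|---|---|
| 5% | 0.975/0.975 | 1.00 |
| 10% | 0.950/0.975 | 0.97 |
| 20% | 0.900/0.975 | 0.92 |
| 30% | 0.850/0.975 | 0.87 |

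The spurious reduction is therefore about 3-13%. Admissions divided by person-time give a ratio of about 1.00 in every row.

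**Effect on a t-test.** In 20,000 simulated trials of 40 per arm with Poisson admissions, a t-test on raw counts falsely favoured Arm 1 in 2.4% of trials when exit was equal. At 30% v 5% exit this was 4.8%, 5.6% and 8.2% for assumed rates of 0.3, 0.5 and 1.0 admissions per patient.

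**Exit linked to prognosis.** Assume 0.5 admissions per 24 weeks, a between-patient frailty with variance 1, and a chance of leaving that rises with frailty. Against 5% in controls:

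| Arm 1 exit | Ratio of mean counts | Ratio per person-time | t-test falsely favours Arm 1 |
|---|---|---|---|
| 15% | 0.89 to 0.91 | 0.95 | about 4% |
| 25% | 0.79 to 0.81 | 0.89 | about 7 to 8% |

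The ranges cover different ways of generating exit. Person-time removes about half of this bias, not all of it.

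**Schedule.** Section 4.7 and Appendix 4 record admissions at week 16, and the staffing line of Table 4 budgets assessments of all patients at weeks 16 and 24. Section 4.5 gives controls no attendance between weeks 12 and 24. As written, control admissions in that period are recalled over 12 weeks, while Appendix 4 divides the same period at week 16.

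**The case against.** Four points on the other side carry weight.

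1. A reader might infer that the plan commits to a t-test on raw admission counts. It does not. Objective 2 is descriptive, frequencies are a named summary that suits it, and the t-test sentences speak of results or changes in general. This stands. But the Protocol predicts a between-arm difference and names no other between-group method, and setting raw frequencies side by side has the same weakness.

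2. Follow-up is a common 24 weeks, and the last completed column of Appendix 4 gives approximate time at risk. Appendix 12 also dates each Arm 1 session. This stands in part. Individual follow-up time is not wholly absent, but it is coarse, it is better dated in Arm 1 than in Arm 2, and a blank column does not separate a death from a missed visit.

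3. The bias requires partial totals to be analysed as complete, and the Protocol does not say so. If only completers were analysed and exit were unrelated to prognosis, the ratio would be 1.00. If sicker patients leave, bias remains under either handling.

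4. The size rests on assumed exit gaps. The Protocol assumes 5% dropout with no difference between arms, and visit compensation and home sessions are meant to limit losses. This also stands. The larger visit burden in Arm 1 makes unequal loss plausible but does not establish it.

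Offsets and count models may properly be left to an analysis plan that is not shown. The missing data fields may not.

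**Conclusion.** The concern holds as a gap in data collection with a consequence for the analysis. Admissions are recorded as counts, all-cause death and exit dates are not recorded in either arm, and the one route by which a death is captured is closed to controls. If death or dropout differs between arms, a comparison of raw counts is biased toward the arm that loses more follow-up.

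The spurious difference is about 3-13% for exit of 10-30% v 5% unrelated to prognosis, and up to about 20% at 25% v 5% if frailer patients leave. It is zero under the null with equal exit. All of these figures rest on assumed rates.

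A reader might go further and conclude that deaths would be scored as treatment successes, or that dropout would by itself produce the expected finding. The documents support neither. No success is defined, the bias runs the other way if controls lose more follow-up, and the simulated chance of a falsely significant result in favour of Arm 1 rises from about 2.5% to at most about 8%. The change is worth making because it is cheap and the missing data cannot be recovered later, but the fault does not invalidate the trial.

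**What to change.** - **Appendix 4, both arms:** add a row for date of death, or date last known alive or last contact.
- **Section 6.0:** compare admissions as a rate per person-time, using a Poisson or negative binomial model with log follow-up time as offset. Report the rate ratio with its 95% confidence interval for 0-12 and 0-24 weeks.
- **Deaths:** report all-cause deaths by arm beside the admission result. Use admission or death as a sensitivity analysis, not as a replacement for Objective 2.
- **Schedule:** reconcile section 4.7, Appendix 4 and Table 4 with section 4.5 on week 16, so that admissions are ascertained on the same schedule in both arms.

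The cost is one form row, a vital-status enquiry for patients who stop attending, and a slightly longer analysis. With 40 per arm and probably few events, the interval will be wide and the result exploratory. Person-time will not remove all bias if leaving is linked to prognosis, which is why deaths should be shown alongside.
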